### Statistical analysis plan

For data analysis, the IG-1, the IG-2, and the control group will be compared. All analyses will be carried out using bilateral tests with a nominal significance level of 0.05. However, if the comparisons obtain a *p*-value of less than 0.10, they will also be discussed as indicative of trends. Initially, basal characteristics of all groups will be evaluated to establish homogeneity in age, socio-demographic, comorbidities, laboratory parameters, concomitant medication and diabetes complications. An initial, descriptive comparison between groups of all variables will be performed to evaluate their baseline balance. Statistical significance will be assessed by the chi-square or t-test between the groups. Exploratory analyses will be applied when necessary.

The main variable is set as the difference in mean HbA1c values between the final visit and baseline. The difference will be evaluated in terms of the evolution of HbA1c as contrasted between groups by paired t-Student, or if the assumption of normality is not met for the right non-parametric.

If differences in the characteristics of the patients in each group are observed in the descriptive section of the study, a linear regression of the main variable (parameter evolution during the study) will be adjusted. This linear regression adjusted for the variables identified in the descriptive section, or the ability to adjust the model by setting a propensity score, will be evaluated. For all models, the distribution of waste will be studied, as well as the coefficient of determination (R2), to check for the correct setting.

As was done in Vinagre et al. [4], a subgroup analysis will be performed by a) gender (male / female), b) age: < age 65 / ≥ 65, and c) according to HbA1c control levels (< 10% / ≥ 10%).

We will determine the prevalence of patients who achieved a concentration of HbA1c of less than 7% at the end of the study. A categorical variable (No, Yes) will be calculated. The analysis of a significant decrease in HbA1c will be carried out using a logistic regression analysis adjusting by the effect of the study groups (as *dummy* variable) and the main factors previously determined to be associated with the target of 7% (in a previous descriptive analysis or adjustment by the *propensity score*). The power of discrimination (C statistic and ROC curve) and calibration (Hosmer & Lemeshow test) for the final models will be studied. The software we will use for analysis of the data will be R Core Team (2014). R: A language and environment for statistical computing. R Foundation for Statistical Computing, Vienna, Austria (http://www.R-project.org/).

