## Methods/design

### Aims of the study

Following this line of thought, the aim of this study is to assess whether glycaemic control improves in very poorly controlled type 2 diabetic patients as a result of interventions based on treatment intensification and on an increase in the patients’ adherence to treatment with a diabetes-targeted clinic specifically held for those patients.

The hypothesis is that in patients with inadequately controlled T2DM, a preliminary comprehensive detection intervention developed based on a monographic consultation interview and a complex intervention to improve the self-efficacy of patients could improve the effectiveness and cost-effectiveness in controlling glycaemia and other metabolic and risk factor parameters compared to the usual practice.

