### Study design

A mixed method study will be carried out, which will compare poorly controlled T2DM patients (poor glycaemic control was defined as an HbA1c value > 9% in the last test performed in the 12 months prior to study inclusion), treated with two different comprehensive approaches with a control group receiving only usual clinical care. The mixed methodology for the development of complex interventions composed of two phases: a first phase consisting of a qualitative study carried out through personal interviews with patients and professionals, and a second quantitative phase that will correspond to the execution of the clinical trial and in which the findings of the first phase will be applied.

We designed this study considering that the intervention group 2 will be the control group for Intervention group 1, where the specific monographic consultation is implemented. Group Intervention 1 includes the main intervention for which we will test the effectiveness to improve glycaemic control. In parallel to Intervention group 2, we decided to include an additional comparison group consisting of type 2 diabetic subjects attending primary care centres managed by our institution in our region, with subjects selected according to the same study criteria. To select this latter group, we describe the use of the Sistema d´Informació per al Desenvolupament de la investigació en Atenció Primària (SIDIAP) database, which contains anonymised electronic health records of patients attended at primary care centers of the same health care districts not participating in the study.

This study is non-randomized because it would be difficult give a different treatment to an individual in the same primary care center treated by the same professional without it affecting the outcome in the standard care arm of the study.

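### The main comparator is stated in two ways, and the analysis section compares all three groups at 0.05, with a p < 0.10 trend rule, without carrying a primary contrast forward

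*Protocol article*

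**What the plan says.** Four sections of the protocol article bear on the main comparison.

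- **Aims of the study.** The hypothesis is that the intervention improves glycaemic control "compared to the usual practice". Several secondary aims likewise set the intervention groups against the control group.
- **Study design.** The first sentence also compares the two approaches with a group under usual care. The next paragraph says that "intervention group 2 will be the control group for Intervention group 1", identifies IG-1 as holding the main intervention to be tested, and describes the SIDIAP group as an addition.
- **Sample size calculation.** One two-group contrast is sized (intervention and control, 1% HbA1c, two-sided 0.05, power 80%). The pair is not named.
- **Statistical analysis plan.** "For data analysis, the IG-1, the IG-2, and the control group will be compared". The primary outcome is fixed: "The main variable is set as the difference in mean HbA1c values between the final visit and baseline". It is to be "contrasted between groups by paired t-Student" or by a non-parametric test. The error rule is "All analyses will be carried out using bilateral tests with a nominal significance level of 0.05", and comparisons with a p-value "less than 0.10, they will also be discussed as indicative of trends".

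**The concern.** The two candidate contrasts answer different questions. IG-2 receives everything IG-1 receives except the monographic consultation, so IG-1 versus IG-2 isolates that consultation. IG-1 versus the SIDIAP group tests the whole package against usual care.

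They also differ in credibility. Patients in IG-1 and IG-2 both consent and are both recorded in the e-CRF. The SIDIAP controls are selected from a database, come from non-participating centres and contribute data at months 0 and 12 only. The Discussion itself concedes that volunteers tend to be more motivated, which could favour either intervention arm over database controls.

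If the analysis section does not say which contrast is primary, whichever one crosses 0.05 could be presented as the trial's answer, including the one most exposed to that bias. The trend rule widens the range of results that can be given weight.

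**Working it through.** **1. The plan's own sample size, to see what it was built for.** Inputs from Sample size calculation: difference 1, SD 1.46, two-sided 0.05, power 80%, loss 20%, ICC 0.05, 15 patients per GP.

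- n per group = 2 × [1.46 × (1.960 + 0.842)]² / 1² = 33.5
- Allowing for loss: 33.5 / 0.8 = 41.8, so 42
- Design effect: 1 + (15 − 1) × 0.05 = 1.7
- 42 × 1.7 = 71.4, so 72; and 72 × 9 centres = 648, or 216 per group

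The figures reproduce. They use the full 0.05 on one two-group contrast.

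**2. Three pairwise contrasts.** Inputs: three groups of equal size (216 each, Abstract) and the two thresholds in Statistical analysis plan. Assume no true difference and independent groups. Each contrast is z = (difference of two group means) / (its standard error). At least one |z| exceeds a cut-off c exactly when the studentized range of the three means exceeds √2 × c.

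- c = 1.960: P(range > 2.772) = 12.2%
- c = 1.645: P(range > 2.326) = 22.7%

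A simulation with 4 million draws gave 12.2% and 22.7%. Treating the contrasts as independent would give 1 − 0.95³ = 14.3% and 1 − 0.90³ = 27.1%. That is too high, because the contrasts share groups.

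**3. Two contrasts sharing one group** (IG-1 versus IG-2 and IG-1 versus control). Each difference has variance 2σ²/n and their covariance is σ²/n, so the correlation is 0.5. From the bivariate normal, 1 − P(|z₁| < c and |z₂| < c) is:

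- c = 1.960: 9.1%
- c = 1.645: 17.6%

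**4. Summary, chance of at least one result under the threshold.**

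| Contrasts read as primary | p < 0.05 (significant) | p < 0.10 (trend) |
|---|---|---|
| One | 5% | 10% |
| Two, sharing a group | 9.1% | 17.6% |
| Three | 12.2% | 22.7% |

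These count errors in either direction. If only false benefit counts (IG-1 better than IG-2, IG-1 better than control, IG-2 better than control), the simulated chance at the two-sided 0.05 cut-off is 6.6%, against 2.5% for one contrast.

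**The case against.** The case on the other side has several parts, and some of them stand.

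- **Three pairwise tests are not listed.** A reader might infer from the analysis section that three primary tests are planned. The text says only that the groups will be compared, by a t-test or its non-parametric counterpart. The logistic model for HbA1c below 7% enters group as dummy variables, which usually gives two contrasts against a reference. This stands: three is a reading, and two gives about 9%.
- **A trend is not a claim.** A reader might quote 23% as the chance of a false claim. The plan keeps significance at 0.05, and results under 0.10 are only "they will also be discussed as indicative of trends". This stands: 23% is the chance of reaching the trend label.
- **The ranking is not wholly absent.** A reader might say that IG-1 versus IG-2 has no priority. Study design does give it some, and the two-arm and three-group evaluations have separate sections. This stands in part: the ranking exists, but Aims of the study, Sample size calculation and Statistical analysis plan do not follow it.
- **A fuller plan may settle order and multiplicity, and the Abstract calls phase 2 exploratory.** Silence on testing order is not the point made here. The point is the conflict over the comparator and the stated 0.10 rule, both in this document. The exploratory label lowers the seriousness. It sits beside a stated hypothesis and a formal power calculation.
- **Distinct questions may not need shared alpha.** That is debatable, and the fix does not depend on it.
- **The sample size suffers no harm.** This stands on the plan's own inputs. With 216 per group, 20% loss and design effect 1.7, power for a 1% difference is 99.4% even at 0.05/3 = 0.0167.

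**Conclusion.** The point holds in limited form. The document gives two main comparators, sizes one unnamed pair, and then compares three groups at a nominal 0.05 without applying its own ranking. It also writes in a trend rule that gives weight to results short of significance.

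The size is conditional: about 12% for at least one falsely significant result if all three contrasts are primary, and about 9% if two are. It rests on no true difference, equal and independent groups, and every counted contrast being open to presentation as the main result. It is not the trial's actual error rate. The study is non-randomised, has three health areas per group and takes its controls from a database, so clustering and confounding also affect false positives. The subgroup analyses are not counted either. If the Study design ranking were applied throughout, the error on the primary contrast would be 5% under the same assumptions.

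This should be corrected because it alters what can be concluded, but it does not invalidate the design.

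**What to change.** 1. In Statistical analysis plan, state that the single primary contrast is IG-1 versus IG-2 on change in HbA1c from baseline to 12 months, tested two-sided at 0.05, as Study design indicates.
2. Align the hypothesis in Aims of the study and the first sentence of Study design with this, and name the pair in Sample size calculation.
3. Label the contrasts with the SIDIAP control group as secondary and report them as estimates with 95% confidence intervals.
4. Delete the p < 0.10 rule.

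These are changes of text and add no patients. The real cost is that the comparison with usual practice, which the current hypothesis names, loses primary status. The team should also confirm that 1% is the difference it wants to detect between two arms that differ only in the consultation. On the plan's inputs (216 per group, 20% loss, design effect 1.7), power at 0.05 is 99.8% for 1% and 68% for 0.5%; the 0.5% is my illustration, not a figure from the document.

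A strict fixed sequence (IG-1 versus IG-2 first, then the SIDIAP contrasts) is optional. It would hold the whole family at 5%, but a null first result would block any formal test against usual practice, even if both interventions worked.

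Follow-up was due to end on 31 October 2018 and the article appeared on 7 February 2019. If outcome data had been seen by the time the primary contrast is named, the amendment should say so.

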The secondary aims are to determine:The percentage of patients who achieve HbA1c levels of < 7% and < 8%.The improvement of lipidaemic control measured by the mean concentration of low-density lipoprotein cholesterol(LDL-C), non-high density lipoprotein cholesterol (non-HDL-C), and triglycerides in the intervention groups relative to the control group.Whether the percentage of patients who achieve target levels of LDL-C, non-HDL-C, and triglycerides recommended by the Catalan Health Institute guidelines (REGICOR tables) [14] is higher in the intervention groups than in the control group.Whether the percentage of diabetic patients with mean systolic blood pressure < 140 mmHg and mean diastolic blood pressure < 90 mmHg is higher in the intervention groups than in the control group.Whether the adherence to the screening for chronic complications associated with T2DM, according to the protocol of the Catalan Health Institute (fundoscopy, microalbuminuria, examination of the foot: arterial index and peripheral sensitivity), is better in patients who have participated in the specialized consultation unit than in the control group.Whether the patient’s self-efficacy to implement changes in risk factors is different in intervention group 1 (IG-1) than in intervention group 2 (IG-2).Whether the direct health costs of T2DM patients who participated in the monographic consultation are different from those in the control group.The impact on satisfaction and quality of life of patients.Whether the improvement in the control of behavioural cardiovascular risk factors (smoking and exercise) is better in the intervention than in the control groups.The improvement in the adequacy and intensification of treatment (clinical inertia).

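### Ten or more secondary comparisons with usual care are each tested at an unadjusted 0.05, with p < 0.10 discussed as a trend and no statement that they are only supportive

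*Protocol article*

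**What the plan says.** The Statistical analysis plan section gives one error rule for the whole study: "All analyses will be carried out using bilateral tests with a nominal significance level of 0.05". It then adds a second tier: "if the comparisons obtain a *p*-value of less than 0.10, they will also be discussed as indicative of trends". It also fixes how many groups are involved: "For data analysis, the IG-1, the IG-2, and the control group will be compared".

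Aims of the study puts more than HbA1c into the hypothesis, namely that the interventions "could improve the effectiveness and cost-effectiveness in controlling glycaemia and other metabolic and risk factor parameters compared to the usual practice". The secondary aims then list, among others:

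- "The percentage of patients who achieve HbA1c levels of < 7% and < 8" percent;
- for lipids, "mean concentration of low-density lipoprotein cholesterol(LDL-C), non-high density lipoprotein cholesterol (non-HDL-C), and triglycerides in the intervention groups relative to the control group";
- attainment of the LDL-C, non-HDL-C and triglyceride targets;
- the share of patients with blood pressure under 140/90 mmHg, which is asked to be higher with intervention than in controls;
- smoking.

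HbA1c, lipids, blood pressure and smoking all have a SIDIAP source for the control group in Table 1. The Abstract calls phase 2 exploratory. The Statistical analysis plan section does not carry that label over to the secondary aims; it only says that exploratory analyses will be applied when necessary, which reads as extra, unspecified work.

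**The concern.** A per-test level of 0.05 is harmless for secondary outcomes when the plan also says that they support the primary result and carry no claim of their own. Here the text goes the other way. Every comparison gets the full 0.05, and results that miss it are promised a discussion as trends down to 0.10. With this many outcomes and two intervention groups, chance alone can readily supply a significant or trending lipid, blood-pressure or smoking result. Because the hypothesis names metabolic and risk-factor parameters, such a result could be presented as partial confirmation even if HbA1c did not move.

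This is a stated rule, not a gap. A fuller analysis plan could add a hierarchy or a label, but it would have to override the trend sentence.

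**Working it through.** **1. The plan's own error figures.** The sample size section uses two-sided 0.05, power 0.80, SD 1.46, a difference of 1% HbA1c, 20% loss and a design effect of 1.7.

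- n = 2 × [1.46 × (1.960 + 0.842)]² / 1² = 33.5 per group
- 33.5 / 0.8 = 41.8, so 42
- design effect 1 + 14 × 0.05 = 1.7; 42 × 1.7 = 71.4, so 72

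This matches the stated 72. Level and sidedness agree with the analysis section, and the calculation covers one outcome, HbA1c. The document states no family-wise error rate.

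**2. Counting the secondary outcomes with control data** (secondary aims against Table 1):

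- HbA1c below 7% and below 8%: 2
- mean LDL-C, non-HDL-C, triglycerides: 3
- target attainment for the same three lipids: 3
- blood-pressure control, taken as one outcome: 1
- smoking: 1 (exercise has no SIDIAP source)

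The total is 10. Screening items (about three) and direct costs are also set against control and are left out, so ten is a low count. Two intervention groups against control give up to 20 comparisons.

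**3. Independent tests, one group against control.** With every null true, the chance of at least one false positive is 1 − (1 − α)^k.

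- α = 0.05, k = 10: 1 − 0.95^10 = 40.1%
- α = 0.10, k = 10: 1 − 0.90^10 = 65.1%
- false benefit only at 0.05 (0.025 per test): 1 − 0.975^10 = 22.4%
- false benefit only at 0.10 (0.05 per test): 1 − 0.95^10 = 40.1%

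**4. Allowing for correlation and the shared control.** Ten equicorrelated normal endpoints were simulated in three equal arms (400,000 replicates, all nulls true), with each intervention arm compared with the same control. The correlation ρ is an assumption, since the protocol gives none. A false benefit is a rejection in the favourable direction only.

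| Threshold | Contrasts with control | Error counted | ρ = 0 | ρ = 0.3 | ρ = 0.5 | ρ = 0.8 |
|---|---|---|---|---|---|---|
| 0.05 | one | either direction | 40% | 35% | 29% | 17% |
| 0.05 | two | either direction | 61% | 55% | 46% | 29% |
| 0.10 | one | either direction | 65% | 58% | 49% | 30% |
| 0.10 | two | either direction | 85% | 80% | 71% | 49% |
| 0.05 | one | false benefit | 22% | 18% | 14% | 9% |
| 0.05 | two | false benefit | 37% | 29% | 24% | 15% |
| 0.10 | one | false benefit | 40% | 31% | 25% | 15% |
| 0.10 | two | false benefit | 60% | 47% | 38% | 25% |

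**5. Sensitivity to the count.** The HbA1c aim names no comparator. If the below-8% outcome is dropped, k = 9 and 1 − 0.95^9 = 37.0%, so the result barely moves. The below-7% outcome stays, because the analysis section models it with study group as a term.

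**The case against.** The best defence is that these are ordinary secondary outcomes. HbA1c change is the one named main variable and the only one powered. The Abstract calls phase 2 exploratory. The level is described as nominal, which means per test. Results between 0.05 and 0.10 are called trends, not significant effects. The aims are framed as things to determine, and several are not directional: costs and self-efficacy are asked to be different, and self-efficacy compares the two intervention groups with each other. Unadjusted secondary testing is common where no confirmatory claim is made, and a condensed article may leave ordering or adjustment to a fuller plan.

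Most of this stands, and it sets the severity. The missing hierarchy is not itself the fault. What remains is that the exploratory label never reaches the rule for reading secondary results, while that rule explicitly invites interpretation of p-values up to 0.10.

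A reader might infer that a false secondary claim is more likely than not. The documents do not support that. Ten comparisons at 0.05 reach 40% at most. Passing one half needs both intervention groups with modest correlation, or about 14 independent tests (1 − 0.95^14 = 51%), or counting trends as claims, which the plan does not do. For a false benefit, only one of the 16 scenarios above passes one half: both groups, the 0.10 tier and zero correlation. Zero correlation is implausible for LDL-C, non-HDL-C and their own target versions.

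A reader might also infer that the Discussion contradicts the exploratory label, because it foresees implementation if effectiveness is shown. That remark is conditional, concerns metabolic control as a whole, and makes no confirmatory claim for any secondary outcome.

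**Conclusion.** The concern holds in a limited form. The rule as written leaves a real chance of a spurious secondary finding. At 0.05, a false benefit arises with probability 22% to 9% for one group against control and 37% to 15% for both, against 2.5% for a single test. The trend tier raises these to 40% to 15% and 60% to 25%. Counting either direction gives 40% to 17% and 61% to 29% at 0.05, and 65% to 30% and 85% to 49% at 0.10.

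These figures assume that every secondary null is true, that each test holds its nominal level, that there are ten outcomes, and that endpoints are equally correlated between 0 and 0.8. More outcomes would raise them. The point is minor to moderate: it bears on how secondary results are reported, and the primary HbA1c analysis is not affected.

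**What to change.** In the Statistical analysis plan section:

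1. Delete the sentence that has p-values below 0.10 discussed as trends.
2. Add that the secondary aims are supportive, in line with the exploratory label in the Abstract; that they will be reported as estimates with 95% confidence intervals; and that no claim of effect will rest on an unadjusted secondary p-value.

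This takes one or two sentences and needs no extra patients, data or analyses. The cost is that isolated secondary results can no longer be presented as effects or trends. The level and sample size for HbA1c stay as they are. An HbA1c result between 0.05 and 0.10 would also lose the trend wording, which agrees with the 0.05 on which the sample size was based.

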#### Phase 2: Interventional study

##### Design

A controlled, non-randomized interventional study that involves primary care centres of 3 health care districts in Catalonia (Lleida, Girona, and Barcelona).

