#### Control group

The control group will consist of a randomized selection of patients who meet the inclusion criteria and have the same sociodemographic and clinical characteristics as the patients from the intervention groups, including the three participating health care districts. Patients allocated in this group will receive routine clinical care with the usual control by the family doctor and nurse according to the current Catalan Health Institute protocol. The data of patients in the control group will be obtained from the electronic medical record (SIDIAP) database [23]. The inclusion period for the control group will be from 9 December 2015 (the date when the first patient entered the study) until 31 October 2017 (end of the recruiting period). Data on diabetic status, glycaemia and all other study variables that were recorded in the electronic health records for patients in the intervention groups will be extracted from the SIDIAP database for 12 months for each patient. Participants will be followed up until they experience the outcomes of interest, die, leave the SIDIAP database (e.g., change of address) or complete the follow-up (31 October 2018). If the intervention groups reach the study sample earlier than 31 July 2017, the data for the control group will be followed until 12 months from the date when the last patient would be enrolled in the intervention group.

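### In this non-randomised study the primary HbA1c contrast is adjusted only if baseline differences are observed, which leaves avoidable residual confounding and an open choice of model

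*Protocol article*

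**What the plan says.** The Study design section explains the lack of randomisation: "This study is non-randomized because it would be difficult give a different treatment to an individual in the same primary care center". The Design section of Phase 2 repeats it: "A controlled, non-randomized interventional study that involves primary care centres of 3 health care districts in Catalonia".

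The Statistical analysis plan section then proceeds in three steps.

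1. Baseline characteristics are compared between groups: "Statistical significance will be assessed by the chi-square or t-test between the groups". The general level is set in the same section: "All analyses will be carried out using bilateral tests with a nominal significance level of 0.05".
2. The primary variable, change in HbA1c from baseline to the final visit, is contrasted between groups by a Student t-test (the text calls it paired) or a non-parametric alternative. No covariates enter.
3. Adjustment follows on a condition: "If differences in the characteristics of the patients in each group are observed in the descriptive section of the study, a linear regression" is fitted to the HbA1c change. Its covariates are those that the descriptive comparison picks out. A propensity score is mentioned as another possibility to be evaluated.

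For the proportion reaching HbA1c below 7%, the logistic model is always adjusted. Its covariates are the "main factors previously determined to be associated with the target of 7" per cent, as found in a prior descriptive analysis, or a propensity score.

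On design-stage control, the Control group section says that the database controls will "have the same sociodemographic and clinical characteristics as the patients from the intervention groups". It names no matching variables or method.

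**The concern.** Without randomisation, differences between groups in prognostic factors are expected, and a non-significant baseline test does not show that they are absent. Bias from a covariate depends on its imbalance multiplied by its effect on the outcome. A gate on observed imbalance ignores the second factor, and at this sample size it often misses small imbalances. Confounders that are missed stay in the primary estimate.

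The rule also leaves the primary model to be settled after the data are seen. It may be an unadjusted test, a regression on whichever variables were flagged, or a propensity-score analysis. No covariate is fixed for the primary outcome, not even baseline HbA1c. At stake are a somewhat biased primary estimate, a type I error above the nominal 5%, and a result that others cannot tell apart from the most favourable of several candidates.

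**Working it through.** **Inputs from the protocol article.** Sample size calculation: two-sided alpha 0.05, power at least 80%, difference 1 HbA1c point, common SD 1.46, 20% loss, intra-class correlation 0.05, 15 patients per GP, 72 per centre, 648 in total. Abstract: 216 per group.

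**The plan's own figure.**
- n per group = 2 × [1.46 × (1.960 + 0.842) / 1]² = 33.5.
- With 20% loss: 33.5 / 0.8 = 41.8, so 42.
- Design effect: 1 + (15 − 1) × 0.05 = 1.70.
- 42 × 1.7 = 71.4, so 72. Then 72 × 3 = 216 per group and 216 × 3 = 648.

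The stated sample size is reproduced, and the point does not change it.

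**How often a baseline test flags a true imbalance.** For an imbalance of d SD and n per group, the standard error is √(2/n) and the chance of p < 0.05 is about Φ(d/√(2/n) − 1.96). At n = 216, √(2/216) = 0.0962. For d = 0.10, Φ(1.04 − 1.96) = 0.18. For d = 0.20, Φ(2.08 − 1.96) = 0.55.

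| True imbalance | 0.10 SD | 0.15 SD | 0.20 SD | 0.30 SD |
|---|---|---|---|---|
| 216 per group | 18% | 34% | 55% | 88% |
| 72 per group | 9% | 14% | 22% | 44% |

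At 216 per group, a confounder imbalanced by 0.10-0.20 SD therefore goes unadjusted in about 45-82% of studies.

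**What that does to the estimate.** The documents give no imbalances or prognostic strengths, so these are assumptions: K = 1 or 5 independent confounders, each imbalanced by 0.10-0.20 SD, all acting in one direction, jointly explaining R² = 20-40% of the variance of HbA1c change. The SD of change is taken as 1.46 and the true effect as zero. Each coefficient is 1.46 × √(R²/K), so the expected unadjusted bias is 1.46 × d × √(K × R²). For K = 5 this runs from 1.46 × 0.10 × √1 = 0.146 to 1.46 × 0.20 × √2 = 0.413. The simulation (2,000 runs per setting, no clustering) agrees with this.

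| 216 per group | Bias, K = 1 | Type I error, K = 1 | Bias, K = 5 | Type I error, K = 5 |
|---|---|---|---|---|
| No adjustment | 0.06-0.18 | 8-24% | 0.15-0.42 | 18-84% |
| Adjust only where p < 0.05 | 0.03-0.06 | 6-7% | 0.08-0.13 | 8-14% |
| Fixed full set | about 0 | 5-6% | about 0 | 4-6% |

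With 173 per group (216 × 0.8, after the assumed loss), the test-based rule with five confounders gives bias 0.08-0.15 and type I error 8-16%.

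**The case against.** **Design-stage control.** Areas are to be chosen with similar characteristics, all groups share the HbA1c entry criterion, and database controls are to resemble intervention patients. This may well reduce imbalance. But no matching method or variables are given, and the selection of controls does nothing for IG-1 versus IG-2, which the Study design section presents as the test of the main intervention.

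**The gate is inferred.** The condition is that differences are observed, with no numerical threshold. That is true. The significance-test reading is the natural one because the tests come just before, but it remains a reading. If no threshold was meant, the analyst's discretion is wider.

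**The detail belongs in a fuller plan.** A covariate list might. But the article states a rule, conditional and chosen from the data, and the objection here is to that rule.

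**The effect is small.** The rule removes much of the confounding, and what remains is well below the 1-point target. This stands and limits the claim.

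Three stronger readings are tempting and are not supported:

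- *Bias of 0.3-0.55 points, up to half the target.* A reader might take the largest imbalance that just escapes the test, 1.96 × √(2/216) = 0.189 SD, multiply by a correlation of 0.3-0.5 and by 1.46 to get 0.083-0.138 points, and then by four covariates. The correlations are not in the documents. Four independent covariates at 0.5 would explain 4 × 0.25 = 100% of the variance, which is degenerate. At 0.3 they explain 36% and give 0.33 points, but only if all four just escape in the same direction. With true imbalances of 0.189 SD the chance that all four escape is about 0.5⁴ = 6%.
- *Ignoring clustering hides imbalance.* Tests that ignore positive clustering flag more differences, not fewer.
- *The HbA1c < 7% model may go unadjusted.* It is always adjusted; only its covariate set is open.

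**Conclusion.** The point holds in a limited form. The plan ties adjustment of the primary contrast to observed baseline differences and leaves both the covariate set and the choice between regression and propensity score to be settled from the data. That is a poor rule for a non-randomised comparison.

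Under the assumptions above, it leaves residual bias of roughly 3-6% of the target difference with one confounder and 8-13% with five, and raises the type I error to about 6-14%. A covariate set fixed in advance removes this when it contains the confounders.

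These sizes rest on assumed imbalances and prognostic strengths, on confounders all acting in one direction, on p < 0.05 as the gate, on 1.46 as the SD of change (the protocol calls it only a common SD), and on ignoring clustering. Confounders acting in opposite directions would partly cancel. The weakness of the baseline tests depends only on the group size and the 0.05 level. The openness of the model choice depends on none of these assumptions.

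**What to change.** Before any outcome analysis, name one adjusted model as the primary analysis of HbA1c change, to be used whatever the baseline comparison shows.

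- **Covariates.** Fix them from variables available in all three groups: baseline HbA1c, age, sex, diabetes duration, BMI, baseline antidiabetic medication and Clinical Risk Group, all in Table 1 with a database source for controls, plus health care district. District is not in Table 1 but is known by design.
- **Method.** Either the regression or one fully specified propensity-score analysis, built without outcome data, may be primary. State which, and make the other the sensitivity analysis.
- **HbA1c target endpoints.** Use the same covariate set for the < 7% and < 8% endpoints, in place of factors selected for their association with the outcome.
- **Baseline table.** Report it descriptively, with standardised differences, and do not use it to decide whether or for what to adjust.

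The cost is a change of wording in the analysis plan. The variables are already collected and the sample size is unaffected.
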